### Randomization

Randomization to a control group or an intervention group will be conducted using a remote web-based concealed computer-generated randomization system organized through Tayside Clinical Trials Unit (TCTU). To minimize the likelihood of imbalance between groups, for each site we will stratify according to age (≤60 years, 61 to 80 years, and ≥81 years), gender and disability. Disability will be assessed using routinely collected data from the Barthel Index [35], a scale measuring independence in activities of daily living. The maximum score is 100, indicating independence. Participants will be stratified according to scores that indicate likelihood of independence in activities of daily living (0 to 40, 45 to 55, 60 to 100) [36]. Tayside Clinical Trials Unit (TCTU) will set up a password-accessed online randomization system that will be accessed only by research staff. After baseline assessment, the study researcher will enter stratification details. The system will determine random allocation after which the artists will be informed.

### Intervention

The CEI protocol for the trial has been developed from an existing art program. Tayside Healthcare Arts Trust has delivered a creative engagement program involving visual art to stroke survivors receiving in-patient rehabilitation in Tayside over several years - the Tayside Creative Engagement Intervention (TCEI). The intervention is delivered by artists who are experienced in working with patient populations to facilitate creation of artwork. To prevent contamination with the current trial, that program, which provides one 12-week intervention annually in each unit, will be suspended for the trial duration.

We used data from qualitative interviews with stroke survivors, artists and rehabilitation staff who had previously participated in TCEI to define the intervention components and to model the TCEI for use in the trial. The qualitative phase enabled us to define five discrete intervention stages and their components, and to identify the outcomes likely to be associated with each stage. The stages provide a framework within which the artist’s work, whilst still allowing them to adapt the specific art activities and materials to the needs and interests of individual participants.

Stage 1 involves meeting with artist to discuss interests, stroke and define initial creative goals. Participants’ interests and preferences will be discussed, and knowledge about their state of health and stroke-related impairments will be obtained and recorded in a participant profile. In Stage 2, participants will be introduced to materials and mark making (drawing, collage, printing, painting and mixed-media techniques). This stage will ascertain participants’ ability to handle art materials and their expectations of the process, and provide them with an introductory experience of working with materials. Stage 3 enables participants to move from materials and mark making to developing personal project ideas and goals. Here the artist will guide the participant in use of the materials and how to consider content or subjects that are of personal interest to them. In Stage 4, the participant will control and direct the expression of content and the artist will instruct and facilitate the creative process of interpretation to allow development of personal project ideas into creative finished pieces. Finally, in Stage 5 the artist and participant review the completed work; and the artwork is mounted and displayed within the ward setting for viewing by staff, relatives and other patients. The achievement of a completed creative piece of work to provide a tangible output will lead to the discussion of further ideas which can be progressed by repetition of the intervention stages, supported by the artist. The artist protocol is described in Additional file 1.

### Artist training

Two professionally qualified visual artists who have previously delivered participatory arts programs in healthcare settings will provide the intervention. The artists involved in delivering the intervention have previously delivered arts programs in healthcare settings. Prior to the commencement of the study, the artists will be introduced to trial procedures and the structured intervention in a workshop setting. The artists will be trained in each stage of the intervention protocol and in how goals are developed, plans for achievement made and progress reviewed during each intervention stage. The artists will be required to record participants’ attendance, intervention stage and progression, and record observations of all processes and material and equipment use. The artists will also be trained in the completion of study documentation and the need to maintain blinding. The research manager, a study co-applicant and artist with 15 years of experience working in healthcare settings with stroke survivors and other clinical populations will deliver their training along with the study researchers.

### Intervention procedures

Stage 1 of the intervention involves a discussion and exploration of participants’ interests, preferences, and physical impairments, which the artist will record in a participant profile. This background information will be used to negotiate initial creative goals. The artist will use their expertise and training to collaborate with the participant, to tailor the equipment and media to participants’ impairments and preferences for the topic and nature of the work they wish to undertake. Preferences, based on participants’ interests, occupation, life experiences and previous experience of art will be explored in the initial session and at each subsequent point of progression to ensure that the materials and the topic for creative exploration, is tailored to the individual.

Materials will be individually selected to match participants’ impairments based on their physical ability to handle the materials and their ability to comprehend a process (for example, reverse text in printmaking) to produce a piece of artwork. A range of visual arts materials will be available to the artist and participant, including drawing and painting media, printmaking equipment, three-dimensional modelling clay and craft-based construction materials. These materials present different approaches to art-making that the artist will tailor to match participants’ interests, abilities and impairments. The approaches include two-dimensional mark making using pencils or paintbrushes on paper, two-dimensional printmaking, three-dimensional modelling and three-dimensional craft techniques (weaving, felting and mosaic). All materials and equipment are available from a good online arts and crafts retailer. Modifications to the materials or provision of supplementary equipment will be undertaken as necessary to enable the participants to handle them (for example, providing pencils of brushes of wide diameter to facilitate grip, provision of left-handed scissors or use of anti-slip mats to facilitate one-handed working).

Artistic goals will be set and jointly reviewed by the artist and the participant at each of the intervention stages, and the processes of art-making and the nature of the finished product will be tailored according to progress. To achieve goals, each participant will receive a maximum of four group and four one-to-one sessions with the artist. Group sessions were selected because the social benefits of group interaction during art have previously been shown to be effective [25, 27]. There is also evidence that one-to one sessions with the artist are beneficial for engagement [26]. For these reasons, both modes of delivery will be selected. Participants will engage with the artist over three to five weeks to a maximum of eight sessions. This duration was selected as it reflects the average length of stay of stroke patients in these rehabilitation centers. Participants will have the opportunity to attend at least two sessions per week. The individual sessions will last up to one hour and the group session will last up to one hour and 30 minutes.

During these sessions participants will be progressively taken through the five intervention stages, within which activities and art materials will be adapted and artwork progressed according to personal interests and abilities. Participants may repeat one or more stages a number of times during the course of the intervention duration. When the participant achieves stage 5 in the intervention the artist will review that work and negotiate with the participant to agree at which of the five stages the participant would like to next engage. This may be stage 2 (exploring different materials), stage 3 (developing a new idea or theme) or stage 4 (further work based around an already established idea or theme).

The artists will monitor participants’ progress closely throughout the trial and complete a sessional log of progress, events, material use and other pertinent observations. This log will be reviewed on a monthly basis to establish if any intervention modifications are required. The completion of study documentation will also be monitored on an ongoing basis by the research manager and research associate and will be assessed and reported at the end of the study.

The intervention will take place within two inpatient stroke rehabilitation units at a large wheelchair accessible table(s) in an appropriate location not used for other rehabilitation activity or therapy. All equipment utilized will also be appropriate to this setting (table-top easel, cutting mat and so on). Sessions will be delivered face-to-face by the trained artist as one-to-one sessions with individual participants, between Monday and Friday. To ensure that art participation does not encroach on individual rehabilitation therapies (physiotherapy, occupational therapy and speech and language therapy), which are delivered Monday to Friday, the group sessions with up to a maximum of five participants, will be convened at the weekend, depending on recruitment rates.

The intervention is in addition to usual rehabilitation. Usual rehabilitation includes, depending on need, half an hour per day of physiotherapy, occupational therapy and speech and language therapy. The intervention protocol is included as Additional file 1. At the end of the study, participants will be provided with details of community programs that people with stroke can attend after hospital discharge. When reporting study findings for publication, we will follow the Template for Intervention Description and Replication (TIDieR) checklist [37].

### Control group

Control participants will receive the same usual rehabilitation as the intervention group. Reflecting usual practice within the units, art made by previous participants will be available for viewing. After baseline assessment and randomization, the control group will receive from the study researcher a portfolio of work produced by previous participants of the Tayside CEI, with details of the community programs that people with stroke can attend after hospital discharge. Participants will be given the portfolio and invited to view it during their rehabilitation stay. Prior to outcome assessment, the study researcher will visit participants again to answer questions and to discuss options for community programs, if the person is interested.

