**Methods/Design:**

This trial is a two arm, single-blind, randomized controlled feasibility trial within in-patient stroke rehabilitation. We will recruit 80 patients receiving stroke rehabilitation in two stroke units in a health board area of Scotland (40 patients in each arm). Intervention arm participants will receive a visual-arts based CEI facilitated by experienced artists. Artists will follow an intervention protocol with specific components that enable participants to set, achieve and review artistic goals. Participants will receive up to eight intervention sessions, four within a group and four one-to-one with the artist. Control group participants will receive usual care only.

Data collection will occur at baseline, post-intervention and three-month follow-up. Stroke-related health status is the primary outcome; mood, self-esteem, self-efficacy, perceived recovery control and hope are secondary outcomes. Semi-structured interviews will be conducted with purposively selected patients, artists and healthcare staff to elicit views and experiences of the intervention and feasibility and acceptability of trial processes. Recruitment rates, retention rates and patient preference for art participation will also be collected. Data will indicate, with confidence intervals, the proportion of patients choosing or refusing participation in the CEI and will allow calculation of recruitment rates for a future definitive trial. Summary data will indicate potential variability, magnitude and direction of difference between groups. Findings will inform sample size calculations for a definitive trial. Thematic analysis of qualitative data will be managed using the Framework Approach. Framework is an analytical approach for qualitative data, commonly used in policy and medical research.

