### Specific objectives

The objectives of this study are to examine the feasibility of intervention delivery in a trial context in two stroke rehabilitation units; to examine the feasibility of the trial processes, recruitment, retention and outcome assessment; and to provide estimates of the effect size of the intervention compared to usual care, in order to inform the development of a full-scale trial

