## Methods/Design

We will conduct a single-blind randomized controlled feasibility trial [30]. People with a diagnosis of stroke consecutively admitted to two stroke rehabilitation units in northeast Scotland will be screened for trial inclusion within one week of their admission to rehabilitation. Those meeting inclusion criteria and agreeing to participate will be randomized to an intervention group who will receive the CEI for up to eight sessions with an artist, or a control group that will receive an art portfolio to view. Outcomes will be examined at the end of the intervention and at three-month follow-up.

The rehabilitation units provide rehabilitation services to stroke survivors following discharge from acute stroke units. Admission to a rehabilitation unit typically occurs less than two weeks after stroke onset, and the average rehabilitation stay is 35 days. In the rehabilitation unit, survivors receive occupational therapy, physiotherapy and speech and language therapy as part of their usual care. The CEI will be additional to those therapies

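### The control arm gets more than usual care, and its earlier community-programme information may confound the three-month difference

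*Protocol article*

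**What the plan says.** The comparator is described in two ways.

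- **As usual care.** The abstract (Methods/Design) states "Control group participants will receive usual care only". Specific objectives sets out "to provide estimates of the effect size of the intervention compared to usual care".
- **As usual care plus something else.** The opening of the main Methods/Design section has "a control group that will receive an art portfolio to view". The Control group section adds that, once randomized, "the control group will receive from the study researcher a portfolio of work produced by previous participants of the Tayside CEI", and that this comes "with details of the community programs that people with stroke can attend after hospital discharge". A second contact follows: "Prior to outcome assessment, the study researcher will visit participants again to answer questions and to discuss options for community programs". The sentence then limits the discussion to people who are interested. Statistical analysis labels the control condition as viewing art, and the Qualitative phase section calls it a control intervention.

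For community-programme information outside the Control group section, the only statement is under Intervention procedures: "At the end of the study, participants will be provided with details of community programs that people with stroke can attend after hospital discharge". It does not define the end of the study for an individual, and it does not say whether one arm or both are meant.

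**The concern.** Two things follow if the article is carried out as written.

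First, the objective promises a contrast with usual care, but the trial estimates a contrast with usual care plus a portfolio, programme details and a researcher visit. A later trial that takes the label at face value could plan for a different comparator from the one studied.

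Second, controls are told about programmes open to them after discharge before their first outcome assessment, while the intervention arm appears to be told only once its outcomes are complete. The time when attendance is possible is largely the follow-up interval. If attendance differs by arm and affects any outcome, the three-month difference mixes the effect of the art intervention with that of the programmes. Under Statistical analysis, the between-group difference is reported at both time points, the mixed models generate the power calculations for the definitive trial, and the size of the difference is one criterion for choosing its primary outcome. A systematic shift would therefore be passed on.

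**Working it through.** The article states no figure on this point, and Sample size calculation says no formal calculation was made, so there is nothing to reproduce. The check is a comparison of sections, then timeline arithmetic, then a test of whether a size can be derived.

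**1. Is the control more than usual care?** The Control group section ties one element to usual practice in the units: earlier participants' art being available to look at. It does not say this of the portfolio brought by the researcher, the programme details or the second visit. The word "only" in "Control group participants will receive usual care only" therefore conflicts with the article's own description.

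**2. When does each arm get the programme details?**

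Inputs:
- Controls: details after baseline and randomization (week 0), and a visit before an assessment held at four weeks or at discharge if sooner (Control group; Trial procedures).
- Intervention arm: engagement over three to five weeks (Intervention procedures), assessment after eight sessions or at discharge if sooner, and follow-up three months later, taken as 13 weeks (Trial procedures).

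| Reading of end of the study | Intervention arm informed | Lag after first control contact | Lag after second contact (by about week 4) |
|---|---|---|---|
| After own three-month follow-up | 3 + 13 = 16 to 5 + 13 = 18 weeks | 16 to 18 weeks | 16 − 4 = 12 to 18 − 4 = 14 weeks |
| End of own intervention | 3 to 5 weeks | 3 to 5 weeks | about zero (3 − 4 = −1 to 5 − 4 = +1 week) |

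The first reading is the more natural one. The Qualitative phase section uses the same expression for the point at which participants are contacted for interview, and places those interviews after the three-month assessment. If the sentence under Intervention procedures covers both arms, controls still have the details from week 0, so the asymmetry remains.

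**3. Does the gap cover a period when attendance is possible?** The programmes are for use after discharge. The average stay is 35 days, or 35 / 7 = 5 weeks, and patients are identified within about a week of admission. Most of the time between discharge and the last assessment is therefore follow-up time.

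**4. Can a size be derived?** To first order,

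bias at three months = (difference in programme uptake between arms) × (programme effect, in SD).

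The article gives neither factor, nor the sign of the second. With assumed uptake differences of 10 to 50 points and assumed effects of 0.2 to 0.5 SD, the product runs from 0.10 × 0.2 = 0.02 SD to 0.50 × 0.5 = 0.25 SD in absolute value. A range this wide, resting wholly on assumptions, is an illustration and not an estimate.

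For scale, the 95% confidence half-width for a difference in means at 40 per arm is 1.96 × √(2/40) = 0.44 SD, before dropout or covariate adjustment. To show how a shift would carry forward, take an assumed true difference of 0.40 SD, 80% power, two-sided 5%, and n per arm = 2 × (1.96 + 0.84)² / d². This gives 99 per arm. If the observed difference were lower by an assumed 0.06 SD (0.34 SD), the same formula gives 136.

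**The case against.** The strongest reply has four parts.

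- **The real control is disclosed.** The main Methods/Design section and the Control group section describe it openly, and viewing art is linked to usual practice. This stands: the fault is an inconsistent label, not concealment, and rewording cures that part.
- **No harm is shown.** A reader might infer that the three-month contrast is contaminated, or that it shrinks by some fixed percentage. The article does not support either. It gives no uptake or effect, does not say the programmes are art programmes, and makes the discussion conditional on interest. Exposure of controls to the existing art programme is dealt with by suspending that programme (Intervention section). A fixed percentage would also require the programmes to reproduce the full effect of the art intervention and nobody in the intervention arm to attend. This stands, and limits the point to possible confounding.
- **The timing is inferred.** A reader might also take the control visit to fall immediately before the self-report measures. The text says only that it precedes the assessment. Nor is it certain that the intervention arm hears nothing until after follow-up, because the end of the study is undefined. This stands in part: the Qualitative phase wording favours the later reading without settling it.
- **It is a feasibility trial.** No definitive hypothesis test is planned, and the illustrated shifts are smaller than the 0.44 SD half-width. This lowers the stakes but does not remove them: imprecision does not excuse an avoidable systematic difference in an estimate meant for planning.

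The Qualitative phase will ask controls about changes in behaviour and the effect of the control intervention on later life. With three controls interviewed, that can explore uptake but not measure it. Whether attendance is captured on a case report form may be left to the full protocol, so its absence from the article is not held against the plan.

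**Conclusion.** The concern holds in two limited respects. The abstract and the objective misdescribe the comparator, which is usual care plus a researcher-delivered art portfolio, community-programme details and a further researcher visit with optional discussion. In addition, the arms appear to receive the programme details at different times, so the three-month difference may be confounded by a differential co-intervention.

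The second part assumes that the end of the study falls after each participant's three-month assessment, giving a lag of about three to four months. On the alternative reading the lag is zero to five weeks and the concern largely falls away. The size and direction of any bias are unknown, and no dilution figure follows from the article. The matter is worth correcting because the affected contrast informs the next trial and the correction costs little.

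**What to change.** 1. Give the same community-programme details to both arms at the same trial time point, for example both at discharge or both after the three-month assessment.
2. Under Intervention procedures, state when the details are given and to which arms.
3. In the abstract and Specific objectives, restate the comparator as usual care plus viewing an art portfolio, adding community-programme information if it is kept.
4. If timing cannot be aligned for participants already enrolled, record community-programme attendance in both arms at the three-month assessment and interpret that contrast accordingly. Study timeline runs follow-up to November 2014, after the article's September 2014 publication, so some assessments may still be open to this. Otherwise the aligned timing can go into the design of the definitive trial.

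The cost is some rewording, a shift in when one set of details is handed out, and at most one extra question. The downside is small: one arm receives the information earlier or later than now planned.
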